### Participant identification / recruitment strategy and randomization

Patients are recruited from neurological practices and outpatient clinics in Bavaria, Berlin, Brandenburg, Hesse, Baden-Württemberg, Schleswig-Holstein, North Rhine-Westphalia and Mecklenburg-Western Pomerania in Germany. Patients of a centre who fulfill the inclusion criteria and for whom there are no reasons for exclusion are consecutively included in the study. After information and obtaining consent to participate, patients are randomized into the intervention and control groups.

Concealed randomization with variable block length takes place at the patient level using an online tool implemented in the electronic health record system. The allocation sequence is generated by the UMG.

Patients can be enrolled via managed care contract with the participating health insurance companies or via a direct treatment contract with the physician (without the participation of a health insurance company).

### Study centres

The study centres take on essential functions in the area of patient recruitment (patient information, informed consent), the management and documentation of study-relevant procedures, data collection, and the forwarding of data, in addition to intervention-related services. Each practice receives detailed training with the study procedures in the context of virtual training sessions before the start of patient inclusion.

Physician practices or participating providers are reimbursed for enrolment and performance of individual intervention services on a per-service billing basis. The individual services provided per patient and the corresponding remuneration are presented transparently for the service providers via the patient platform used and invoiced to the project management. The preliminary calculation of compensation is primarily based on estimates of the time required for single services.

### Intervention

A MS-specialized neurologist examines the cognitive and physical status of the MS patient using standardized assessments like the Symbol Digit Modalities Test (SDMT) [6], Expanded Disability Status Scale (EDSS) [7], 9-Hole Peg Test (9-HPT), and Timed 25-Foot Walk (T25-FW) of the Multiple Sclerosis Functional Composite (MSFC) [8–10] every six months. Additionally, as part of a quarterly consultation on health, affective, and participation status, the neurologist examines health-associated participation and workability. The quarterly medical consultation by the neurologist includes participation-, deficit- and resource-oriented therapy planning as well as progress monitoring with regard to health-associated participation and the preservation of the working ability. In addition, it serves to ensure the stabilization of the current treatment success and the optimization or adaptation of the therapy.

As a result, the neurologist identifies risks that influence health status, workability status, family status, and social status due to the living environment. Together with the patient, the physician discusses possible treatment options to improve health and prevent workability as well as plans therapy. The neurologist initiates and coordinates the interventions with other health care providers (e.g. occupational physician, psychologist, rehabilitation physician, pension insurance, health insurance company) based on the patient’s needs. After the intervention has taken place, or if additional treatment needs have been identified by the service providers during the intervention, the neurologist and the corresponding service provider can hold a teleconsiliary discussion on the findings to ensure the success of the treatment and to discuss the therapy goal. If the neurologist identifies an acute risk of incapacity or reduction in earning capacity during his*her examination, he*she can initiate a case conference together with the other players involved to discuss possible treatment options for acutely avoiding incapacity and loss of participation. The patient can be included in the case conference to ensure treatment adherence.

The neurologist has different treatment options to improve health and workability. If the treating neurologist identifies:health risk from employment and risk for disease exacerbation, the neurologist initiates an *occupational health examination* by a qualified occupational physician. The focus of the occupational health examination is to identify health destabilizing influences and to reduce them by occupational medical interventions tailored to the patient’s needs.deficits in coping with the disease during the examination that contribute to worsening health: the neurologist can initiate *disease education*. The focus is on teaching environmental and behavioral strategies for better coping with MS. Patient education promotes active engagement with MS and activation of self-efficacy and knowledge building. Patient education is offered by MS-specialized neurologists or MS-specialized neuro-psychologists, depending on regional needs. The counseling neurologists and neuro-psychologists are to be qualified by a specialized training module.risk of or present restriction for participation due to MS or symptoms accompanying MS (affective, cognitive disorders, physical deficits, etc.), which cannot be eliminated, compensated, or minimized by the previous interventions, the neurologist initiates *an inpatient, day-care, or outpatient rehabilitation* in an MS-specialized rehabilitation centre, depending on the patient’s need.a negative influence of the social and family environment during his examination, the neurologist initiates individual *psychosocial and legal counseling*. The focus of the consultation is on the individual identification of challenges in the family and social environment, support in determining and enforcing legal claims, and support offers. The counseling, support, and close follow-up help to improve health and reduce or eliminate the burden of the disease. Depending on the regional situation, counseling is provided by the MS self-help organization or medical assistant within the neurological practice. The counselors are qualified by proven MS-specific knowledge as well as by a qualified degree as a social worker; the medical assistant will be qualified by an appropriate advanced training module.

### Control condition

In the first 12 month, participants in the control group will not receive trial-related healthcare interventions, but “treatment as usual”, i.e. the standard healthcare as currently applied in the MS standard treatment in Germany. This comparator was chosen because the research question is whether the new intervention affects outcomes like days of incapacity of work, quality of life, and cost-effectiveness and for this a comparison to “usual care” is warranted.

However, patients in the control group do also receive interventions after 12 months at the same frequency as participants in the intervention group (Fig. 2).

**Fig. 2 Fig2:**
[figure not shown]
*Flow of participants in MSnetWork.* * The quarterly medical consultation by the neurologist includes participation-, deficit- and resource-oriented therapy planning and progress monitoring with regard to health-associated participation and the preservation of the working ability. In addition, it serves to ensure the stabilization of the current treatment success and the optimization or adaptation of the therapy

### Electronic health record

Networking and documentation, as well as data exchange between the players involved, take place by using an electronic health record. The online platform contains relevant data on the patient’s MS-associated health data and information and results on assessments for functional capacity as well as examinations from occupational physicians. In addition, the platform in which the patient’s record is embedded makes available group offers for disease education recognizable for the coordinating medical assistant of the neurological practice to enable rapid scheduling and therapy assignment. The data exchange is based on the already existing and legally provided structures of the patient’s electronic health record, is used only after the patient’s consent, is browser-based, and has the necessary interfaces for demand-oriented care.

### Outcomes

#### Primary outcome

The primary outcome is the number of MS-associated sick leave days at 12- and 24-month follow-ups. These data will be provided by the routine data of the health insurance funds. In addition, the days of incapacity to work will be collected with a baseline and follow-up patient questionnaire every six months, as well as via the digital patient file during the quarterly consultations (intervention group) or the functional assessments (control group). Self-reported primary data can be used for the analysis of patients with and without secondary data from the health insurance funds (inclusion via managed care contract or treatment contract), but are somewhat more susceptible to information bias in direct comparison (e.g. self-reporting bias, recall bias) [11].

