**Methods:**

The MSnetWork study is designed as a multicenter randomized controlled trial, with two parallel groups (randomization at the patient level with 1:1 allocation ratio, planned *N* = 950, duration of study participation 24 months). After 12 months, the patients in the control group will also receive the interventions. The primary outcome is the number of sick leave days. Secondary outcomes are health-related quality of life, physical, affective and cognitive status, fatigue, costs of incapacity to work, treatment costs, out-of-pocket costs, self-efficacy, and patient satisfaction with therapy.

Intervention effects are analyzed by a parallel-group comparison between the intervention and the control group. Furthermore, the long-term effects within the intervention group will be observed and a pre-post comparison of the control group, before and after receiving the intervention in MSnetWork, will be performed.

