### Sample size

The calculation of sample size was done for the analysis of the primary outcome “number of sick leave days” per patient within 12 months. The calculation assumes that the difference in sick leave days is to be an average of 5 days (or 20% of the average sick leave days for MS patients in Germany) between the intervention and the control group. This number is deduced from the German statistics on types of illness [5], with an annual average number of 25 days of incapacity to work due to MS among the statutorily insured persons. Further, based on a database analysis of the insurances taking part, up to 50% of the insured persons with MS do not have any days of incapacity to work in a 12-month observation period. Hence, the number of cases is calculated with a regression model for count data with “zero inflation”.

Depending on the assumption about the proportion of insured persons without sick leave days (30% vs. 50%), with a statistical power of 80%, and a 2-sided significance level of 0.05, the minimum sample size necessary to identify a group difference for the primary outcome of sick leave days is between 600 and 860. An expected drop-out of 20% in the course of the twelve-month comparison period leads to an increase in the net case numbers to the gross case numbers of *N* = 750 and *N* = 1075 (Table 1).

**Table 1 Tab1:** Results of the calculations for determining sample size

Patients without days of incapacity to work within 12 months (in %)	Net number of cases	Gross number of cases^a^
30% 50%	600 860	750 1.075

^a^Drop out of 20% in 12 months

Therefore, we aim for an initial gross sample size of 950 cases in total (475 cases per group). This number of cases is somewhat closer to the upper limit and would thus make it possible to achieve the planned power even if the actual conditions deviate from the assumptions made.

The strategies to achieve adequate recruitment to reach the target sample size had been.

based on the number of patients being treated in the past in the neurological practices who would have fulfilled the eligibility criteria. Neurological practices will be identified with the help of the BDN, the Professional Association of Neurologists.

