Additionally, the intervention’s implementation potential into the standard care system will be examined, because even if it can be demonstrated that patients benefit from the new form of care, this alone is no guarantee that it will be adopted as standard care. In that way the implementation potential is assessed through:(14)Interviews and surveys with service providers (e.g. doctors, psychologists, nurses, medical assistants) on the acceptance of the intervention. This analysis aims to record supporting and hindering factors during the project period as a secondary outcome because the knowledge of these factors is a basic prerequisite for the subsequent implementation in regular care.(15)Intervention costs: For the study period the individual interventions are remunerated to the service providers at flat rates. Based on time records and surveys, the actual costs of the individual interventions are determined to examine whether the compensatory allowances when transferred to standard care will ensure adequate future financing for the service providers even after the project duration.

The patients’ primary and secondary data are linked via a patient pseudonym. For this purpose, a trustee agency is involved.

Endpoints, outcomes, sources, and follow-ups are presented in detail in Table 2.

**Table 2 Tab2:** Endpoints, outcomes, sources, and follow-ups

	Outcome	Measurement instrument or data source	Follow-ups
PRIMARY	Number of sick leave days	Routine data from the SHI funds Patient questionnaire and digital patient health record	-^*)^ Month 0, 6, 12, 18, 24 (and during quarterly consultations)
SECONDARY	Costs of the incapacity to work	Routine data from the SHI funds Human capital or friction costs approach based on primary data for sick leave days	-^*)^ Month 0, 6, 12, 18, 24 (and during quarterly consultations)
	Treatment costs/ frequency: • Inpatient care • Outpatient care • Rehabilitation • Medication • Remedies • Therapeutic appliances • Others	Routine data from the SHI funds Patient questionnaire	-^*)^ Month 0, 6, 12, 18, 24
	Out-of-pocket payments	Patient questionnaire	Month 0, 6, 12, 18, 24
	Implementation potential into standard care: • Acceptance • Intervention costs	Interviews and survey of service providers Process analysis, time records and surveys	Study month 24 & 36 Study month 12–36

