## Discussion

To the best of our knowledge, this is the first study to consider multidisciplinary care in MS patients and its effects on health, gainful employment, and sick leave in Germany. In the project, patients with MS receive a bundle of interventions aiming to positively influence their ability to work and to participate in a self-determined life. The neurologist at the centre of the newly established network coordinates the care services offered by various service providers and, for the first time, works together with a preventive occupational physician. Tele-consultations and case discussions support this cooperation.

This complex intervention needs a highly integrated collaborative evaluation of health and health economic effects. In that way, primary and secondary data will be primarily matched, but due to the extensive collection of primary data within the project, a comprehensive evaluation of the new intervention is possible even in the absence of secondary data. The patient questionnaire and the documentation of MS-specific days of incapacity to work by the treating neurologists within the digital patient file make sufficient data available to analyze the primary endpoint, costs of incapacity to work and the course of treatment independently.

Complementing the patient perspective and the social and occupational participation outcomes achieved through the interventions, the perspective of service providers is also highlighted. Even though the new and comprehensive care for MS patients with the managing neurologist in the middle of the network can be understood as an innovation that goes beyond the current level of care. It is therefore of central importance that the new form of care is seen as useful and reasonable by the providers on the one hand, and that adequate financing can be ensured in the future on the other. The determination of the actual costs is thus indispensable for the transfer of this pilot implementation within the framework of MSnetWork.

Against this background, the study aims to improve the current employment situation of MS patients, considering disease-specific, therapeutic, psychosocial, and socioeconomic factors and the providers’ perspective to ensure such future treatment for MS patients.

If the project proves to be a success, a transfer for the treatment of other chronic diseases with an impact on the ability to work is conceivable and desirable.

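### The primary outcome is limited to MS-associated sick leave in some sections and not in others, and the sample size's mean and zero share are not shown to describe the same count

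*Protocol article*

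**What the plan says.** All references are to the protocol article.

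**Definition**
- Primary outcome section: "The primary outcome is the number of MS-associated sick leave days at 12- and 24-month follow-ups". Insurer routine data are the source. A six-monthly questionnaire and the digital patient file are collected in addition.
- Abstract, Methods: "The primary outcome is the number of sick leave days".
- Section on sample size, opening sentence: "The calculation of sample size was done for the analysis of the primary outcome “number of sick leave days” per patient within 12 months".
- Table 2, primary row: "Number of sick leave days".
- Discussion: the questionnaire together with "the documentation of MS-specific days of incapacity to work by the treating neurologists within the digital patient file" is said to give enough data to analyse the primary endpoint independently.

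**Sample-size inputs**
- Mean, from national statistics: "annual average number of 25 days of incapacity to work due to MS". The target difference is 5 days, or 20%.
- Zero share, from the participating insurers' database: up to 50% of insured persons with MS "do not have any days of incapacity to work in a 12-month observation period". Table 1 uses 30% and 50%.

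**Recording in the digital file**
- The Primary outcome section places the entries at quarterly consultations in the intervention group and at the functional assessments in the control group. The Intervention and Secondary outcomes sections make those assessments six-monthly.

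**The concern.** A reader cannot tell from the article which days count towards the primary outcome. This has three consequences.

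1. **The count may depend on the source.** The insurer data are described under Secondary outcomes (item 13) simply as sick leave days, the questionnaire as days of incapacity, and the digital file as MS-specific days. Patients enrolled by direct treatment contract have no insurer data, so their outcome must come from the latter two. The definition could then differ by enrolment route.
2. **Cause may be attributed with knowledge of the arm.** The neurologist examines the patient and plans and coordinates the intervention, and so knows the allocation. If file entries are used, that person's record decides which days are MS-specific, with more frequent recording in the intervention arm than in the control arm during the 12-month comparison. The plan acknowledges information bias for self-report only.
3. **The sample size may combine two different counts.** The mean is tied to MS; the zero share carries no such limit and comes from another source. The required N is sensitive to the zero share.

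**Working it through.** **Step 1. Reproduce the plan's figures.** Gross N = net N / (1 − 0.20): 600/0.8 = 750 and 860/0.8 = 1,075. Both match Table 1.

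The net N cannot be rebuilt from the stated inputs. One attempt is a zero-inflated Poisson with overall means 25 and 20, zero share p, L = mean/(1 − p) and variance (1 − p)·L·(1 + p·L). At two-sided 0.05 and 80% power:
- p = 0.3: variances 292.9 and 191.4; N per arm = 7.849 × 484.3/25 = 152.05, rounded up to 153; total 306 (Table 1: 600).
- p = 0.5: variances 650 and 420; N per arm = 7.849 × 1,070/25 = 335.9, rounded up to 336; total 672 (Table 1: 860).

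Other variants also failed to match. The dispersion is not given, so this does not show Table 1 to be wrong. It does mean that any extrapolation has to start from Table 1 itself.

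**Step 2. How Table 1 depends on the zero share.** Patients with at least one day: 600 × 0.70 = 420 and 860 × 0.50 = 430. Table 1 therefore behaves almost as a fixed requirement of about 425 patients with leave, so net N ≈ 425/(1 − p).

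**Step 3. Reserve at the planned size.** 950 × 0.8 = 760 analysed. Power ≈ Φ(2.802 × √(760/N) − 1.96).
- 30% zeros, N = 600: about 88%.
- 50% zeros, N = 860: about 75%.

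Setting 425/(1 − p) = 760 gives p ≈ 0.44, so 80% power holds up to a zero share of about 44%.

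**Step 4. What logic says about the share.** A patient with no day of any cause also has no MS-associated day. If the insurers' share is for any cause, the MS-associated share is therefore at least that large. How much larger cannot be derived from the document.

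**Step 5. Illustration.** The zero shares here are assumptions; the article gives no MS-specific share.

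| Assumed zero share | Net N = 425/(1 − p) | Gross N (÷ 0.8) | Power at 760 |
|---|---|---|---|
| 60% | about 1,060 | about 1,330 | about 66% |
| 70% | about 1,420 | about 1,770 | about 54% |

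The zero-inflated Poisson formula of Step 1, with means held at 25 and 20, moves in the same direction: net 994 at 60% and 1,532 at 70%.

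**Step 6. The other definition.** If all sick leave is intended, the mismatch moves to the mean: 25 days is worded as due to MS, and an all-cause mean in the same persons cannot be lower.

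**The case against.** The strongest reply is that there is no contradiction. The Primary outcome section defines the outcome; the abstract, the sample-size text and Table 2 use a short label for it. No section says all-cause, and the Discussion repeats the MS-specific wording. This stands in part: a reader might infer that the plan sets MS-associated leave against all sick leave, but the other sections are unqualified, not explicitly all-cause.

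On the sample size, the phrase about not having any days may simply mean having none of the MS days just mentioned. The sentence directly follows the MS-specific mean. This also stands: the wording does not prove an all-cause query. Even with an all-cause share, the insurers' figure is an upper bound, and a share of 30–40% could correspond to an MS-associated share still within Table 1. The zero shares of 60% and 70% have no source in the article, and the constant of 425 is read from two table rows and extended beyond them.

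On attribution, insurer data are named as the source and the other data come in addition. The article speaks of documentation by the neurologist, not of a judgement. The questionnaire item is not shown and may carry the same restriction. As a condensed article, it may leave operational rules to the full protocol.

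These replies limit the conclusion but do not remove it. The Discussion says the endpoint can be analysed without insurer data, using the file. That source records MS-specific days and has a different schedule in each arm. The label and the definition still differ in the sections that fix the outcome and size the trial.

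**Conclusion.** The point holds as an inconsistency in the cause restriction, together with sample-size inputs that are not shown to refer to the same outcome. As written, the counted days can differ by source, and a clinician who knows the arm can in effect attribute cause on a schedule that differs by arm.

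A reader might go further and conclude that Table 1 does not apply, or that 80% power is missed because of this mismatch. The article does not support that, because it gives neither the cause basis of the zero share, nor an MS-specific share, nor the dispersion. The supportable statement is that Table 1 is not shown to apply to the outcome defined in the Primary outcome section and that the required N may be understated. The size is conditional: about 66% power at 760 analysed if the zero share is 60% and about 425 patients with leave are needed, both of which are assumptions. If the insurers' share is already MS-specific, this part of the point has no effect on N.

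**What to change.** 1. Use one definition, with the cause restriction stated or removed, in the abstract, Sample size, Primary outcome and Table 2.
2. If MS-associated days are kept, take attribution from the coded diagnosis on the insurer's sick-leave record where available. The article does not say that the supplied data set carries a diagnosis per episode, so this must be confirmed. An insurer-only rule would leave out direct-contract patients; for them, use an identically worded questionnaire item on the same schedule in both arms, not the neurologist's file entry.
3. State the cause basis of the 30–50% zero share. Give the mean and the zero share for the same outcome, and restate Table 1 and the power at 760 if they differ.
4. Report all-cause sick leave days as a sensitivity analysis, since it does not depend on attribution of cause.

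The cost is wording changes in four places, a check of the questionnaire item, one clarification or repeat of the insurers' query, and one additional analysis. The restated power may be less favourable.

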	Reduction in earning capacity: •Subjective prognosis of gainful employment • Employment situation	Subjective prognosis of gainful employment scale (SPE) Patient questionnaire	Month 0, 12, 24 Month 0, 12, 24
	Physical status	Expanded Disability Status Scale (EDSS) Multiple Sclerosis Functional Composite (MSFC: T25-FW, 9-HPT)	Month 0, 6, 12, 18, 24
	Cognitive status Affective status Fatigue	Symbol Digit Modalities Test (SDMT) Depressions-Anxiety-Stress-Scale (DASS) Fatigue Scale for Motor and Cognitive Functions (FSMC)	Month 0, 6, 12, 18, 24
	Health-related quality of life	Multiple Sclerosis Quality of Life (MSQoL)-54 instrument EuroQol-questionnaire (EQ-5D-5L)	Month 0, 6, 12, 18, 24
	Patients’ adherence to therapy	Adherence Assessment Questionnaire (AAQ)	Month 0, 6, 12, 18, 24
	Self-Efficacy	Coping Self-Efficacy Scale (CSES)	Month 0, 6, 12, 18, 24
	Patient satisfaction with the new intervention	Client Satisfaction Questionnaire (ZUF-8)	Month 12, 24

*) Continuous recording within the claims data of the statutory health insurers

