### Statistical analyses

The primary analysis will be performed as an intention-to-treat, ITT, analysis.

A regression model for count data with “zero inflation”, i.e. with a large proportion of cases without incapacity to work, is used to analyze the primary outcome. For this purpose, the zip command in the statistical package STATA is used. The statistical analyses of the other outcome variables are performed with generalized linear mixed-effects models [24].

These models are appropriate for the analysis of cross-sectional and longitudinal data on primary and secondary outcomes, which may be continuous (cost, quality of life) or categorical (early retirement) variables. Interdependencies between measurements in longitudinal data can be appropriately handled by including mixed effects. The application of the regression models to variables with different scale levels is made possible by the appropriate choice of the link function (e.g. identity for continuous variables, logistic for dichotomous variables) and the error distribution (e.g. normal distribution for continuous target variables, binomial distribution for dichotomous variables).

For data analysis with generalized linear mixed models, corresponding procedures are available in all relevant statistical packages (e.g. SPSS, SAS, Stata, R). Beyond these advantages of the chosen analysis model, it should be emphasized that with these models it is possible to specify and statistically test relevant hypotheses about the group, time, period, and interaction effects. These models also allow the handling of missing follow-up data.

For the analysis of cost data, special gamma regression models can be used according to the distributional properties of the dependent variable. With the help of suitable methods, the dispersion of costs and efficiencies is explained, i.e., those parameters are determined which have a significant influence on the costs and efficiencies of the measures.

Cost-benefit analysis: Based on the intervention costs and the saved costs (if applicable), the profitability of the measures is determined. In addition, the difference between intervention costs and the potentially saved costs for MS patients is compared to the effectiveness of the measures (cost-effectiveness analysis), to give information on the intervention’s advantageousness compared to other health policy instruments.

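### The article names no baseline term in the primary model although sick leave days are collected at month 0, and at the protocol's own 50% zero share the planned 950 gives about 75% power, not 80%

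*Protocol article*

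**What the plan says.** All references are to the protocol article.

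- **Primary outcome:** besides routine insurance data, "the days of incapacity to work will be collected with a baseline and follow-up patient questionnaire every six months". Table 2 lists month 0 for this source. For the routine data, its footnote says "Continuous recording within the claims data of the statutory health insurers".
- **Statistical analyses:** the primary outcome is analysed by intention to treat with a zero-inflated count regression, and "the zip command in the statistical package STATA is used". No covariates are listed, and the model is not described as unadjusted.
- **Sample size:** the calculation is made "with a statistical power of 80%, and a 2-sided significance level of 0.05". The target effect is stated as "the difference in sick leave days is to be an average of 5 days (or 20% of the average sick leave days for MS patients". It is derived from an "annual average number of 25 days of incapacity to work due to MS among the statutorily insured persons". The insurers' own data show that "up to 50% of the insured persons with MS do not have any days of incapacity to work in a 12-month observation period". The net requirement is 600 at 30% zeros and 860 at 50%, or 750 and 1,075 gross with 20% drop-out. The plan is 950 gross, with the assurance that this would secure the planned power even under departures from the assumptions.

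**The concern.** In a chronic disease, earlier sick leave is a natural candidate predictor of later sick leave. The trial measures it at month 0, yet the article mentions it neither in the primary model nor in the sample size. If it is left out of the model, between-patient variation that could have been explained stays in the comparison.

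This would be a minor matter in a trial with power to spare. Here the planned number lies below the protocol's own requirement for one of its two scenarios, while the text reassures the reader that power is safe. A baseline covariate is one of the few remedies that needs no further recruitment. If it is not fixed in advance, adding it later looks like a choice made after seeing the data.

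**Working it through.** **1. Reproduce the plan's gross numbers.** Gross = net / (1 - 0.20): 600 / 0.8 = 750 and 860 / 0.8 = 1,075. Both match Table 1.

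**2. Patients left for analysis.** 950 x 0.8 = 760. That is 160 above the 600 needed at 30% zeros and 100 below the 860 needed at 50% zeros.

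**3. Power at 760.** The article gives no dispersion, so the net figures cannot be rebuilt from first principles. Power is scaled from the protocol's own statement that the net number gives 80% at two-sided 0.05:

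Power = Phi[(1.960 + 0.842) x sqrt(760 / N_req) - 1.960]

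- 50% zeros: Phi[2.802 x sqrt(760/860) - 1.960] = Phi(0.674) = **75.0%**
- 30% zeros: Phi[2.802 x sqrt(760/600) - 1.960] = Phi(1.193) = **88.4%**

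**4. Zero share up to which 80% is kept.** Linear interpolation gives 0.30 + 0.20 x (160/260) = 42%. The requirement in patients with sick leave is nearly constant (600 x 0.7 = 420; 860 x 0.5 = 430). Holding it fixed gives 1 - 430/760 = 43% to 1 - 420/760 = 45%. The planned power therefore holds up to about 42% to 45% zeros, not to 50%.

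**5. What baseline adjustment could return.** In a linear model, a baseline covariate with correlation r to the outcome multiplies the required number by (1 - r^2). The documents give no r, so the range is an assumption.

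| Assumed r | Net number needed, 860 x (1 - r^2) | Power at 760 |
|---|---|---|
| 0 | 860 | 75.0% |
| 0.2 | 826 | 76.7% |
| 0.3 | 783 | 78.8% |
| 0.4 | 723 | 82.0% |
| 0.5 | 645 | 86.0% |

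Break-even for 80% at 760: r = sqrt(1 - 760/860) = 0.34.

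**6. Does this carry over to the named model?** Under zero-inflated Poisson with default standard errors, the precision of the count part follows from the fitted means alone. The number per group is about 2.802^2 x (1/m1 + 1/m2) / [(1 - p0) x (ln 0.8)^2], where p0 is the zero share and m1, m2 are the count-part means.

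- p0 = 0.5 and overall means 25 and 20 (count-part means 50 and 40): 7.85 x 0.045 / (0.5 x 0.0498) = 14.2, so 15 per group and 30 in total.
- Reading 25 and 20 as the count-part means themselves: 58 in total.

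Both are far below 860. The protocol's figures imply further overdispersion (a negative binomial dispersion of about 0.62 to 0.66), which default zip standard errors do not reflect. With those standard errors there is no residual variance for a covariate to reduce.

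A simulation under assumed settings pointed the same way. Adjustment reduced the standard deviation of the log ratio of overall means, compared robustly, from 0.114 to 0.099, a variance ratio of (0.099/0.114)^2 = 0.75. It did not narrow the zip count coefficient. Because the settings are assumed, this shows direction, not size.

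**The case against.** The strongest objection is that an article's silence is not a decision. This is a condensed protocol, no analysis plan is shown, and covariate lists are commonly left to that plan. A reader might infer that the primary analysis is unadjusted. The documents do not say so, and the missing covariate list alone would be no finding. This objection stands in full.

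A reader might also infer that adjustment would restore the stated power. That is not supported either. The correlation is assumed, a value of 0.3 still leaves power just under 80%, (1 - r^2) is a linear-model result, and it does not transfer to zip with default standard errors.

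Availability is also less secure than it looks. The article does not promise claims from before enrolment, and it does not give the look-back of the month-0 questionnaire. Patients enrolled by direct treatment contract have no fund data. Mixing claims with self-report would bring in the information bias that the Primary outcome section itself acknowledges.

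The 50% share is an upper figure, and at 30% power is comfortable. But 50% is one of the protocol's own two scenarios, so the shortfall there contradicts its own assurance.

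No parallel request is made for the secondary mixed models. They can carry month 0 as a repeated measure, and patient satisfaction (ZUF-8) has no baseline, being measured only at months 12 and 24.

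**Conclusion.** The point holds in a limited form. Two parts are firm:

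- Month-0 sick leave days are collected, and the article's description of the primary model contains no baseline term.
- At the protocol's own 50% zero share, 760 analysed patients give about 75% power, so the assurance in the Sample size section is not correct for that scenario. This rests only on the protocol's net numbers, its 20% drop-out and normal-approximation scaling.

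The gain from adjustment is plausible but not established. It would be roughly 2 to 11 percentage points for an assumed correlation of 0.2 to 0.5, and only under an analysis whose standard errors reflect the variation between patients. That the trial has chosen an unadjusted analysis cannot be concluded from these documents.

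**What to change.** 1. **Statistical analyses:** state, here or by reference to the analysis plan, that baseline sick leave days are a prespecified covariate in both parts of the primary model. One workable form is log(1 + month-0 questionnaire days), with one source and one stated look-back for all patients and a missing-value indicator.
2. **Same section:** specify robust standard errors, or make the primary contrast a comparison of overall means. Without one of these, the covariate brings little under zip with default standard errors.
3. **Sample size:** replace the general assurance with the power at 760 analysed patients, about 75% at 50% zeros and about 88% at 30%. If credit is taken for baseline adjustment, state the assumed correlation and show a range.

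The cost is a few lines of wording. No new visit, instrument or patient is needed, provided the questionnaire's look-back is the same for everyone. If the analysis plan already contains the covariate, the first item reduces to a cross-reference. The change should be dated before any comparison of outcomes by group.
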